## Abstract

Cognitive behavioral therapy (CBT) is the most successful protocol in gambling disorder (GD) treatment. However, it presents some weaknesses, especially concerning relapse prevention (RP). RP is one of the most important therapeutic steps, aiming at managing cravings and to avoid future relapse increasing perceived self-efficacy. Encouraging results come from the blending of psychotherapy and virtual reality (VR), containing gambling cues. The goal of *Alter Game* (approved by the Ethical Commission, Prot. No. 69346) is verifying the efficacy of an innovative psychological treatment for GD based on the integration of traditional CBT therapy and an immersive VR cue exposure therapy using a serious virtual game, which is a game designed for purposes other than entertainment. RP in virtual cue-exposure therapy allows pathological gamblers to manage the urge to gamble and to avoid relapse by becoming aware of which internal and external triggers are related to craving. We hypothesize that the integrated intervention will be more effective than simple CBT with regard to self-efficacy, craving, and gambling-related distortions. Four virtual ecological environments were developed, and a virtual app, Exludo, interfaced with a computerized multiparametric acquisition system for biofeedback, was created. A sample of about 60 patients aged between 18 and 65 with GD referring to the Addiction Medicine Unit of Verona (Rossi Hospital) will be recruited. Patients will be randomly assigned to the CBT group (16 CBT sessions) or the CBT + VR group (8 CBT sessions + 8 VR cue-exposure therapy sessions). The MCMI-III, the BIS-11, and the SOGS will be used to evaluate inclusion and exclusion criteria, while the *Gambling Related Cognitions Scale* and the *Multidimensional Gambling Self-Efficacy Scale* will be used to verify changes as a function of the treatment. Craving will be evaluated through VAS, and psychophysiological variables will be assessed through biofeedback. A pre-test/post-test experimental design with a 1-month follow-up will be conducted. This study will examine an innovative psychotherapeutic protocol for GD treatment, and it will help in identifying new virtual tools to increase the efficacy of traditional therapeutic approaches that could also be applied to treat other addictions.

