Keeping this background into account, the present *Alter Game* study was designed. *Alter Game* aims at developing an innovative psychological treatment for GD by using VR and verifying the efficacy of an innovative psychological treatment for GD based on the integration of traditional CBT therapy and VR approach. To that goal, we aimed at creating a virtual serious game to prevent relapse in gambling behavior by increasing self-efficacy in managing craving and emotional states and by reducing perceived gambling craving. Indeed, virtual environments are made *ad hoc* for the exposure of patients to specific gambling cues, directed at the detection and management of craving. We chose self-efficacy and craving as dependent variables because they are key aspects in maintaining abstention from gambling. Gamblers that perceive good self-efficacy in managing cravings present a lower probability to relapse, on the basis of the Marlatt RP model (12); thus, craving itself is an important relapse risk factor to be managed and recognized. On the other hand, perceived self-efficacy is a protective factor against relapse (12). Moreover, in response to the above-described limitations in previous studies applying VR approach to gambling treatment, *Alter Game* aims at evaluating the sense of presence through multiple means: the *Independent Television Commission's Sense of Presence Inventory* [ITC-SOPI (44)]; the use of diaphragmatic breathing to manage craving; the presence of cigarette packs, lit cigarettes, snacks, alcoholic beverages (wine, beer), and wine glasses in the specific virtual environments; the use of biofeedback to measure the psychophysiological activation. Cue reactivity, indeed, is measured across several domains of human functioning. The most commonly collected measures are self-reports that assess craving or the desire for a particular substance and physiological responses, which usually include those controlled by the autonomic nervous system, such as heart rate, skin conductance, and skin temperature (45). Psychophysiological arousal is a potential proxy indicator of craving as a reaction to gambling-related stimuli. Conditioned stimuli associated with gambling could simultaneously elicit both subjective craving and psychophysiological arousal (46).

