Our hypothesis is that an integrated intervention with VR will be more effective than simple CBT for improving self-efficacy and lowering cravings. Furthermore, in line with CBT, we expect gambling-related cognitive distortions to decrease. This goal is very important because gambling-related cognitive distortions mediate the relationship between depressive symptoms and gambling severity (47) and contribute to the maintenance of maladaptive emotional regulation styles to reinforce and support biased beliefs about gambling outcomes and controllability (48).

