## Data Analysis

In general, all the patients' demographic and clinical characteristics will be summarized using descriptive statistical methods. In particular, mean, median, and standard deviations will be used for symmetrically distributed continuous variables, median and interquartile distance for asymmetrically distributed continuous variables, and frequency distributions for categorical variables. Multi-method analysis of craving measurement in order to draw up a physiological and psychometric profile of craving (using biofeedback) will be performed. This analysis will be conducted through linear correlation measures. For the analysis of the efficacy of the training course for the treatment providers, Student's *t*-tests for dependent samples or Wilcoxon's non-parametric test for paired samples will be used. Contingency tables and McNemar tests may also be used. For the analysis of the efficacy of the CBT + VR group compared to the CBT group, a mixed ANOVA will be performed for repeated measures with *Time* as within factor (pre-test/post-test/follow-up) and *Group* as between factor (the CBT + VR group/the CBT group).

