## Discussion

A recent review has confirmed the efficacy of CBT to treat various addiction problems (7) and, especially, GD (9). Several published clinical studies have used VR to treat different psychopathological problems (anxiety, PTSD, depression, etc.), with a lot of them underlining that CBT and VR combined could improve the efficacy of social anxiety disorder and paranoia treatments (22, 24). Indeed, VR is a methodological approach that allows to recreate a realistic ecological representation of craving-eliciting situations (34–36). However, as of yet, no clinical study of CBT and VR in GD treatment has been conducted. Keeping this background into account, the necessity to develop a new study protocol—*Alter Game*– emerged. In detail, *Alter Game* aims at developing an innovative psychological treatment for GD by using VR and verifying the efficacy of an innovative psychological treatment for GD based on the integration of traditional CBT, coupled with a novel VR approach.

Based on previous studies, suggesting that CBT and VR combined are more efficient than CBT or VR only (23, 25), we aim at confirming this evidence in gambling addiction by taking specific target variables into account, such as self-efficacy, craving, and cognitive distortions. We can hypothesize that CBT and VR combined will be more effective than CBT only. In particular, at the conclusion of the psychotherapy sessions, we expect to find a higher increase of self-efficacy and a greater reduction of cravings and cognitive distortions—in terms of effect size—in the case of the integration of CBT and VR. To better evaluate these expected results, we aim at using biofeedback in order to observe and measure the psychophysiological activation associated with cue exposure, which would allow us to overcome the limits of self-report craving questionnaires or craving Likert scales. Moreover, we already implemented a training course for the treatment providers to guarantee a correct administration of the psychotherapy protocol with the patients before the study will start.

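### The planned three-occasion mixed ANOVA does not isolate the post-test difference that the hypothesis names, and no outcome is ranked first

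*Protocol article*

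**What the plan says.** Data Analysis gives one between-arm efficacy analysis: "a mixed ANOVA will be performed for repeated measures". Time enters "as within factor (pre-test/post-test/follow-up) and" Group is the between factor. Pre-test is therefore an outcome level and not a covariate. The section does not say whether Group, Group x Time or a particular contrast decides efficacy.

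The Discussion places the hypothesis at the end of treatment: "at the conclusion of the psychotherapy sessions, we expect to find a higher increase of self-efficacy and a greater reduction of cravings". The Design subsection gives the 1-month follow-up a different job, which is to see whether post-test changes last.

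On outcomes, the Abstract hypothesises that "the integrated intervention will be more effective than simple CBT with regard to self-efficacy, craving, and gambling-related distortions". The Introduction says "We chose self-efficacy and craving as dependent variables because they are key aspects in maintaining abstention from gambling", without ranking the two. Its hypothesis paragraph then says of distortions only that "we expect gambling-related cognitive distortions to decrease". The Discussion again claims superiority on all three.

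Recruitment gives n = 58 for power 0.95 in a mixed ANOVA with effect size 0.40 and a single alpha of 0.05, and a target of about 60. Data Analysis expects at least 80% retention.

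**The concern.** There are two separate problems.

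**Test and question do not match.** The question is whether the arms differ at post-test. The Group effect averages over three occasions, one of which precedes treatment. The Group x Time test responds to any departure from parallel profiles, including change between post-test and follow-up, and uses the baseline by differencing, which is less efficient than covariate adjustment. A significant interaction would need a further contrast to support a post-test claim. A non-significant result on either effect could reflect the choice of test rather than the treatment.

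**Outcomes are unranked.** Superiority is claimed on self-efficacy, craving and distortions side by side under one alpha. If success on any of them counts, the overall error rate is not 5%.

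**Working it through.** **Inputs from the article.** About 60 patients, n = 58, effect size 0.40, alpha 0.05 and power 0.95 (Recruitment); three occasions and two groups (Data Analysis); at least 80% retained, so 0.80 x 60 = 48.

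**Assumptions, because the article gives no SD, correlation or allocation ratio.** SD 1, compound symmetry with correlation r between occasions, 1:1 allocation, no mean difference at pre-test, and 0.8 SD at both post-test and follow-up. The effect size 0.40 is read as Cohen's f.

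**1. The plan's own figure.** For the Group main effect over m = 3 occasions, the noncentrality is f² x N x m / (1 + (m - 1)r). At r = 0.5 and N = 58 this is 0.16 x 58 x 3 / 2 = 13.92 on 1 and 56 df, giving power 0.956. At N = 56 power is 0.9495, so 58 is the smallest even total that reaches 0.95. The Group x Time variants tried at r = 0.5 give 18, 52 or 100. The stated size thus fits the Group main effect.

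**2. What 0.40 means for that effect.** With two groups, f = 0.40 is a difference of 2 x 0.40 = 0.8 SD in the average over occasions. With means differing by (0, d, d), the average difference is 2d/3, so d = 0.8 x 3/2 = 1.2 SD at both later occasions. If d is 0.8 SD, Group power at N = 58 and r = 0.5 is 0.69.

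**3. Three tests compared at N = 48 (24 per arm).** Noncentralities, with n = 24 per arm and d = 0.8:
- Baseline-adjusted post-test: (n/2) d² / (1 - r²), on 1 and 45 df. At r = 0.5: 12 x 0.64 / 0.75 = 10.24.
- Group x Time: (n/2) x (2d²/3) / (1 - r), on 2 and 92 df. At r = 0.5: 12 x 0.4267 / 0.5 = 10.24.
- Group: (n/2) x 3 x (2d/3)² / (1 + 2r), on 1 and 46 df. At r = 0.5: 12 x 3 x 0.2844 / 2 = 5.12.

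| r | Adjusted post-test | Group x Time | Group |
|---|---|---|---|
| 0.3 | 0.81 | 0.66 | 0.70 |
| 0.5 | 0.88 | 0.81 | 0.60 |
| 0.7 | 0.967 | 0.962 | 0.525 |
| 0.8 | 0.995 | 0.996 | 0.49 |

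**4. Other effect patterns, N = 48, r = 0.5** (same order of tests):
- Halved at follow-up (0.8 then 0.4): 0.88, 0.68, 0.38.
- Lost at follow-up (0.8 then 0): 0.88, 0.81, 0.20. Group x Time has the same power here as for a sustained effect, so its significance does not locate the difference.
- Growing after therapy (0.4 then 0.8): 0.35, 0.68, 0.38. The ranking reverses.

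**5. Baseline adjustment against a change score.** The variance ratio is (1 - r²) / (2(1 - r)) = (1 + r)/2. This is 0.65, 0.75, 0.85 and 0.90 at r = 0.3, 0.5, 0.7 and 0.8, so the saving runs from 35% down to 10%.

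**6. Several outcomes at 0.05 each.** Three independent outcomes: 1 - 0.95³ = 14.3%. Two: 1 - 0.95² = 9.8%. With three outcomes correlated at 0.5, simulation gave 12.8%.

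**The case against.** A mixed ANOVA is a valid analysis. The Discussion words the hypothesis as a larger increase or reduction, which is differential change, and Group x Time addresses that. A three-level Time factor also matches the design, which includes a follow-up. Post-hoc contrasts and a multiplicity rule may stand in an analysis plan that is not shown, so their absence from the article is no finding. The power comparison rests on assumed inputs: it vanishes at high correlation and reverses for an effect that grows after therapy.

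Much of this stands, and it limits the point. A reader might infer that the ANOVA itself inflates false positives. It does not: a single Group x Time test kept about 5% in simulation under sphericity (5.2%), and the excess in step 6 comes only from unranked outcomes. A reader might also multiply the error rate by counting every GRCS and MGSES subscale, but the article describes those scales without saying that they will be tested separately. Nor does it settle that there are three comparable outcomes. The Design subsection lists craving at every measurement session in both groups, yet the questionnaire batteries under Intervention and in Table 1 contain no craving scale, and the craving-measurement subsection places it during VR therapy. Hence the range from 9.8% to 14.3%. The distortions wording in the Introduction is looser than in the Abstract and Discussion rather than a flat contradiction.

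What does not fall away is that the article fixes the model and the levels of Time, sets the claim at the end of therapy, and places several outcomes under one alpha. The growing-effect pattern, where Group x Time does better, is not the one hypothesised.

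**Conclusion.** The concern holds in a limited form. The decisive effect is unstated, and neither omnibus effect isolates the post-test difference. If Group decides, as the stated n = 58 suggests at r = 0.5, the loss is large: 0.60 against 0.88 at N = 48 and r = 0.5, for 0.8 SD sustained. If Group x Time decides, the loss for a sustained effect is 15 percentage points at r = 0.3 and 7 at r = 0.5, and practically nothing at 0.7 to 0.8. It is larger if the effect fades by follow-up. All of these figures rest on the assumed effect, correlation, compound symmetry and 1:1 allocation, so the direction for the stated hypothesis at low to moderate correlation is firmer than the size. Separately, claiming success on any one outcome carries up to 14.3% false-positive risk for three independent outcomes, or 9.8% for two. This should be changed, but it does not make the planned test invalid.

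**What to change.** - **Decisive test (Data Analysis).** Make it the CBT + VR minus CBT difference at post-test, adjusted for the pre-test value, with a 95% CI. Use ANCOVA, or the post-test contrast of a mixed model with pre-test as covariate. Take follow-up as the second contrast from the same model.
- **Primary outcome.** Have the authors name one. MGSES is a ready candidate, because it is in the battery for both arms at all three occasions, but the choice is theirs. The others become secondary under Holm.
- **Hypotheses.** State once whether distortions are a superiority hypothesis. Reconcile the passages on where and in whom craving is measured before ranking it.
- **Sample size.** Restate it for the chosen test, with the assumed correlation. As a guide, 0.95 power for 0.8 SD with the adjusted post-test comparison needs 76, 64 or 44 analysed patients at r = 0.3, 0.5 or 0.7, before allowing for drop-out.

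**Cost.** For MGSES and GRCS this is wording only, since their pre-test values are already planned. Craving may need its measurement schedule clarified first. The downside is that the outcomes not chosen become secondary claims, and the restated sample size may not equal 58.

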#### Efficacy Evaluation of the Integrated Intervention

##### Design

We will conduct a pre-test/post-test experimental design with a 1-month follow-up.

Two independent groups to which patients will be randomly assigned will be considered. One group will undergo a traditional CBT treatment of 16 sessions (the CBT group), while the second group will undergo the integrated treatment, consisting of 8 CBT sessions and 8 sessions of psychotherapy based on VR cue-exposure therapy, each with a different environment (the CBT + VR group). Each session will last 1 h. To better control the effects of the training in VR on pathological gamblers, the psychophysiological parameters of craving will be measured through biofeedback and VAS at each session of the training (multi-method measurement of craving).

To verify the efficacy of the intervention, one measurement session is planned before the beginning of the treatment (pre-test), and one at the end of the treatment (post-test). For the assessment of the maintenance of any changes at post-test, an additional measurement is planned 1 month after the end of the treatment (follow-up). The three measurement sessions are planned for both the CBT group and the CBT + VR group. In each measurement session, perceived self-efficacy in managing gambling behavior, craving, gambling-related cognitive distortions, impulsivity, personality traits, and pathological gambling symptoms will be measured in both groups.

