### Recruitment

We will recruit a sample of about 60 patients with GD who are referred to the Addiction Medicine Unit of Verona (G. B. Rossi Hospital). This sample size is consistent with the power analysis we conducted *a priori*. Using G^*^Power software to estimate the sample size that would be necessary to achieve a statistical power of 0.95 for a mixed ANOVA, indeed, revealed that a sample size of *n* = 58 was necessary in order to obtain an average effect size, equal to 0.40 (α = 0.05).

Inclusion criteria will be: (a) being male and female subjects over 18 years of age and under 65 years of age; (b) being addicted to slot machines, scratch cards, lotto, SuperEnalotto (because environments were created with these specific cues); (c) informed consent signature. An inclusion criterion (b) will be evaluated by a clinical interview based on the DSM-5 diagnostic criteria in the first psychological assessment session and by SOGS, which reports the type of gambling games played by gamblers.

Exclusion criteria will be the presence of: (a) antisocial personality traits; (b) borderline personality traits; (c) high levels of impulsivity; (d) thought disorders; (e) delusional disorders. Exclusion criteria (a), (b), and (c) were chosen to identify the presence of gamblers probably categorized as “third pathway” to Blaszczynski and Nower (55) and that, therefore, may be more exposed to risks of relapse following immersive VR exposure to environments with trigger cues. Excluding these patients will allow us to guarantee greater safety for them by administering treatment as usual.

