Moreover, we will pay attention to the issue of an attrition rate. We are expecting to find a retention rate of at least 80% (78, 79) to avoid that participant loss will bias research outcomes. After that, we will check for any significant difference between the two treatment groups (CBT and CBT + VR) to verify if there is a differential attrition rate. In particular, we will compare the average number of meetings attended by the participants between the two treatment groups through *t*-tests, and we will compare the presence of drop-outs across the two groups through Chi-square tests. Moreover, we will determine if there are any significant differences (at the baseline) between participants who will complete the post-test session and those who will not in order to verify if specific subgroups of participants have a higher drop-out risk. This analysis will be conducted separately for each group. If any significant differences between participants of the two treatment groups will be found, we will verify that systematic attrition does not occur and we will conduct the analyses to verify the effects of the two interventions (CBT and CBT + VR) with the participants who completed the baseline and post-test assessments. Those lost to post tests will be excluded. If significant differences between participants of the two treatment groups will be found for the average number of meetings attended and the treatment drop-out, and participants who will complete the post-test session will be significantly different from those who will not, subsequent analyses will be conducted by using the last observation carried forward (LOCF) to assess the effects of attrition. Furthermore, we will examine within-group changes in outcomes as a function of session attendance to assess the effects of intervention non-compliance on outcomes. These subsequent analyses will be conducted, not excluding participants who will be lost to post-test and by imputing values for the follow-up variables for the participants who will not complete the post-test assessment.

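### The efficacy analysis drops patients lost to post-test and adds LOCF only after significant attrition tests, leaving the estimate open to bias from foreseeable unequal drop-out

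*Protocol article*

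**What the plan says.** The efficacy model is given in Data Analysis: "a mixed ANOVA will be performed for repeated measures", with Time (pre-test, post-test, follow-up) and Group as factors. The next paragraph deals with attrition in four steps.

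- **Tests.** Sessions attended are compared between arms by t-test and drop-out by chi-square. Within each arm, completers and non-completers of the post-test are compared at baseline.
- **First condition.** If any significant difference between the two treatment groups appears, the effects are analysed in participants with baseline and post-test: "Those lost to post tests will be excluded".
- **Second condition.** If attendance and drop-out both differ significantly between arms and completers differ from non-completers, then "subsequent analyses will be conducted by using the last observation carried forward (LOCF) to assess the effects of attrition".
- **Attendance.** In addition, "we will examine within-group changes in outcomes as a function of session attendance". The closing sentence says that these later analyses retain patients lost to post-test by imputing values.

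The same paragraph expects at least 80% retention. The Recruitment section ends with a rule that takes patients out of the study after cybersickness in two consecutive virtual sessions. The Discussion calls drop-out high in this population.

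**The concern.** Excluding randomised patients because their outcome is missing gives up the comparability that randomisation provides, unless the loss is unrelated to outcome. The plan's safeguard is a set of significance tests at about 30 per arm, which cannot show that loss is ignorable. Only CBT + VR patients have virtual sessions, so only they can meet the cybersickness exit, and loss tied to one arm is foreseeable from the protocol itself. The check offered when the tests do fire is LOCF, which distorts the arm contrast when loss is unequal and patients improve. At stake is the trial's central comparison of CBT + VR with CBT.

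The conditions are also hard to apply. Any result that meets the second condition also meets the first, nothing is stated for no significant difference, and the first condition reads oddly because a significant difference leads to the completers analysis. The word *no* may be missing.

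**Working it through.** **Inputs from the protocol.** The sample is about 60 (Recruitment: "We will recruit a sample of about 60 patients with GD"). Allocation is random to two groups (Design). Its ratio is not given, so 1:1 and 30 per arm are assumed. Retention is at least 80%, so loss is up to 20%, or 12 of 60. Arm-specific drop-out, size of improvement, correlation and drop-out mechanism are not in the protocol and are assumed below.

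**1. The plan's own figure.** Recruitment gives n = 58 for "a statistical power of 0.95 for a mixed ANOVA", with effect size 0.40 and α = 0.05. Reading 0.40 as Cohen's f, with 3 occasions and an assumed correlation of 0.5, the between-groups test has noncentrality f²·N·m/(1+(m−1)ρ) = 0.16 × 58 × 3/2 = 13.92. Power is 0.956 at 58 and 0.9495 at 56, so 58 reproduces. At 80% retention of 60, N = 48 and noncentrality is 11.52, giving power of about 0.91. The loss of precision is modest; bias is the issue.

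**2. Power of the attrition tests** (exact binomial enumeration of the uncorrected chi-square, 30 per arm).

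| Drop-out | Power |
|---|---|
| 15% vs 25% | 0.16 |
| 10% vs 20% | 0.19 |
| 10% vs 30% | 0.50 |
| 10% vs 40% | 0.80 |

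For 80% power, 10% versus 30% needs 62 per arm and 15% versus 25% needs 250. The within-arm baseline comparison, about 24 versus 6 at 20% loss, has power 0.18 at d = 0.5 and 0.40 at d = 0.8. In simulations at 10% versus 30% loss, all three tests were significant together in only 3% to 10% of trials.

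**3. Completers-only, no true difference.** If a fraction p of an arm leaves and the leavers' mean change is δ below the arm mean, the completers' mean change is too high by δ·p/(1−p). Suppose this happens in one arm only:

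- p = 0.30, δ = 0.3 SD: 0.3 × 0.30/0.70 = 0.13 SD
- p = 0.30, δ = 0.5 SD: 0.5 × 0.30/0.70 = 0.21 SD
- p = 0.20, δ = 0.4 SD: 0.4 × 0.20/0.80 = 0.10 SD
- δ = 0: no bias, whatever p is in each arm

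Simulation (30 per arm, 4,000 runs per scenario) agrees:

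- Loss of 10% in CBT versus 30% in CBT + VR, unrelated to outcome: 0.00 to 0.01 SD.
- The same loss, with poor responders leaving more in both arms: +0.08 to +0.09 SD.
- The same loss, with poor responders leaving more in CBT + VR only: +0.13 to +0.14 SD.
- Loss of 20% in both arms, outcome-related in one only: +0.10 SD, while the chi-square test fired in about 6% of trials.

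**4. LOCF, no true difference.** A patient lost before post-test carries the pre-test forward and has zero change. If both arms improve by μ and loss is unrelated to outcome, the spurious contrast is (1−0.30)μ − (1−0.10)μ = −0.20μ:

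- μ = 0.8 SD: −0.16 SD
- μ = 1.0 SD: −0.20 SD

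With a pre-post correlation of 0.5 (SD of change 1), a change-score t-test rejects in about 10% to 13% of trials instead of 5%. With more loss in CBT + VR this works against CBT + VR, whereas the completers-only bias in step 3 favours it.

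**5. Attendance analysis, if its imputed values are LOCF values.** Drop-outs then have both low attendance and zero change. Assume 30 in one arm, 20% random drop-out, drop-outs attending 1 to 12 sessions, completers 13 to 16, and no true dose effect. A Pearson test then gives p < 0.05 in about 28% (0.8 SD improvement) to 51% (1.0 SD) of trials.

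**The case against.** Several stronger readings are tempting and are not supported.

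- **That p-values choose between completers-only and LOCF for the headline result.** LOCF is introduced for later analyses meant to gauge the effect of attrition. The natural reading is an added sensitivity analysis on top of the completers analysis. The overlap in the conditions may come from one missing word and is then a matter of wording.
- **That the estimate is biased whichever path is followed.** If drop-out is unrelated to outcome, completers-only is about unbiased even at 30% versus 10% loss.
- **That 10% to 13% is the plan's type I error.** It is the rejection rate if LOCF were always applied under the assumed loss and improvement. The plan reaches LOCF seldom.
- **That LOCF gives every drop-out zero change.** This holds only for patients lost before post-test. Someone missing only the follow-up would carry the post-test forward.
- **That the three-occasion ANOVA contradicts the baseline-and-post-test set.** The article does not say how a missing follow-up is handled. Listwise deletion is an inference, and the detail may stand in the full protocol or analysis plan.
- **That the attendance analysis certainly builds in an association.** The imputation method for it is not named, and the attendance ranges in step 5 are assumed.

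These objections narrow the point without removing it. On the reading kinder to the plan, the main estimate is always completers-only, and an analysis that keeps all randomised patients appears only after several weak tests are jointly significant.

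**Conclusion.** The concern holds in limited form. The article fixes an efficacy analysis that leaves out randomised patients without a post-test, in a trial where arm-related loss is foreseeable. It relies on tests with power of 0.16 to 0.50 for drop-out gaps of 10 to 20 points (15% versus 25% and 10% versus 30%). The resulting bias is about zero if loss is unrelated to outcome and roughly 0.1 to 0.2 SD if poor responders leave more in one arm. The LOCF check can itself create 0.16 to 0.20 SD under the assumed 30% versus 10% loss and 0.8 to 1.0 SD improvement. These sizes rest on 1:1 allocation and on assumed drop-out, improvement and mechanism, so they illustrate the exposure and do not predict it. The wording of the conditions needs repair on any reading. The paragraph should be rewritten before outcome data are seen.

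**What to change.** Replace the conditional rule with one prespecified analysis.

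- **Primary:** a likelihood-based mixed model with pre-test, post-test and follow-up all as outcomes, Group by Time effects, and baseline means constrained equal across arms. Every randomised patient with a pre-test then contributes in the assigned arm. A model with the pre-test only as a covariate would drop patients with no later value.
- **LOCF:** delete it. Keep the attendance, drop-out and baseline comparisons as description, not as a switch.
- **Data collection:** ask patients who stop sessions, or who leave the VR treatment because of cybersickness, to complete the scheduled post-test and follow-up questionnaires. This concerns outcome collection only and leaves the treatment exit rule as it is.
- **Sensitivity:** report the completers analysis and one multiple-imputation analysis with a penalty for drop-outs. The mixed model assumes data missing at random and does not remove bias from drop-out that depends on unobserved outcome.
- **Attendance:** analyse observed outcomes only and label the result exploratory.

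The cost is one rewritten paragraph, a standard procedure, slightly more analysis work, the effort of contacting patients who stop, and a missing-at-random assumption that must be stated.
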